## Abstract

**Background:** The rising prevalence of chronic conditions constitutes a major burden for patients and healthcare systems and is predicted to increase in the upcoming decades. Improving the self-management skills of patients is a strategy to steer against this burden. This could lead to better outcomes and lower healthcare costs. Health coaching is one method for enhancing the self-management of patients and can be delivered by phone. The effects of telephone-based health coaching are promising, but still inconclusive. Economic evaluations and studies examining the transferability of effects to different healthcare systems are still rare. Aim of this study is to evaluate telephone-based health coaching for chronically ill patients in Germany.

**Methods/Design:** The study is a prospective randomized controlled trial comparing the effects of telephone-based health coaching with usual care during a 4-year time period. Data are collected at baseline and after 12, 24 and 36 months. Patients are selected based on one of the following chronic conditions: diabetes, coronary artery disease, asthma, hypertension, heart failure, COPD, chronic depression or schizophrenia. The health coaching intervention is carried out by trained nurses employed by a German statutory health insurance. The frequency and the topics of the health coaching are manual-based but tailored to the patients' needs and medical condition, following the concepts of motivational interviewing, shared decision-making and evidence-based-medicine. Approximately 12,000 insurants will be enrolled and randomized into intervention and control groups. Primary outcome is the time until hospital readmission within two years after enrolling in the health coaching, assessed by routine data. Secondary outcomes are patient-reported outcomes like changes in quality of life, depression and anxiety and clinical values assessed with questionnaires. Additional secondary outcomes are further economic evaluations like health service use as well as costs and hospital readmission rates. The statistical analyses includes intention-to-treat and as-treated principles. The recruitment will be completed in September 2014.

**Discussion:** This study will provide evidence regarding economic and clinical effects of telephone-delivered health coaching. Additionally, this study will show whether health coaching is an adequate option for the German healthcare system to address the growing burden of chronic diseases.

**Trial registration:** German Clinical Trials Register (Deutsches Register Klinischer Studien; DRKS) DRKS00000584.

**Keywords:** Chronic conditions, Health coaching, Telephone-based, Economic evaluation, Routine data

\* Correspondence: [[contact]](mailto:[contact])

†Equal contributors

Department of Medical Psychology, University Medical Center Hamburg-Eppendorf, [name], Germany

Full list of author information is available at the end of the article

## Background

### Chronic conditions

The leading causes of death and disability are chronic diseases such as, for example, diabetes mellitus, heart diseases or cancer [1]. Because of the rapid aging of the population, longer life expectancy, and medical progress, chronic diseases are expected to cause over three-quarters of all deaths by 2030 [2]. Additionally, an increasing percentage of patients with chronic conditions are multimorbid [3]. Chronic conditions are a burden for the healthcare system and also for the patients and their families. People with a chronic disease have a reduced potential life span and reduced quality of life [4].

### Handling chronic conditions

Due to the high prevalence of chronic diseases, it is important to find strategies to steer against the increasing burden for patients as well as society. One attempt to handle this burden is to increase the self-management of patients since the course of chronic conditions can be influenced significantly by health behavior changes. Therefore, chronic diseases are at least partially considered to be preventable or modifiable [5]. If patients change to a healthier lifestyle by stopping smoking, drinking less alcohol, doing more exercise or changing dietary behavior, they can actively contribute to preventing and controlling complications from chronic diseases [6]. Active patients show greater adherence, know more about their disease and can achieve improved health [7]. Active involvement and improved self-management skills of chronically ill patients may even reduce healthcare costs [8].

One specific method to improve self-management and patient involvement is health coaching. Aims of health coaching are to improve adherence to health behaviors and to support lifestyle changes in order to prevent a negative course of chronic illness [9]. Besides the education of patients by providing evidence-based information, health coaching includes communication styles that increase the motivation to change risky health behaviors. Common strategies of effective coaching programs are goal setting strategies, motivational interviewing, collaboration with healthcare providers [10] and shared decision-making [11]. Health coaching is tailored to the patients' knowledge and needs. It is an addition to the medical consultation by preparing the patient before the consultation and clarifying relevant questions afterwards [12].

### Telephone-based health coaching

There are many ways to deliver health coaching; one way is coaching by phone, which allows reaching even rural areas and impaired patients. The increasing number of studies that evaluate telephone-based health coaching (TBHC) for chronically ill patients shows promising but also conflicting results. For example, participants of TBHC

have reduced diabetes symptoms as well as lowering depressive symptoms [13] and gaining a better total cholesterol and LDL-value [14]. It seems that TBHC has the potential to reduce the rate of coronary events, like myocardial infarction, coronary artery bypass graft and cardiovascular death [15]. However, there are also some studies showing that there are no improvements regarding targeted clinical outcomes [16]. Furthermore, TBHC can help participants change health behavior [17], enhance self-rated health [18], social functioning, self-efficacy, patient activation and perceived health [13,17].

Economic evaluations are rare and still contradictory to some extent. Studies show that TBHC can reduce the number of contacts to the general practitioner [19], hospitalization rates and healthcare costs [11]. However, other studies show only modest effects on hospital admissions or emergency room visits. Also, these studies show no reduction of utilization and costs accompanied by high costs for the admission of the coaching [20,21].

In summary, the results of studies evaluating TBHC are ambiguous. The clearest effects can be observed with psychosocial and self-reported outcomes, like self-efficacy and perceived health. Considering economic effects and clinical outcomes, results of empirical studies are still inconsistent.

In Germany, health coaching is an innovative approach, and the number of studies evaluating TBHC in Germany is very limited. Long-term effects and cost-effectiveness have not been analyzed yet. However, the patients' acceptance of the intervention is good [22-24]. The TBHC used in this study is based on a TBHC service developed by Health Dialog [11,25] and was implemented by Kaufmännische Krankenkasse Hannover (KKH), a statutory health insurance, in 2007. The coaching was adapted to the German patients' requirements after assessing the needs in a previous study [22].

The German healthcare system is contribution-financed and based on self-government and solidarity. The healthcare delivery is not centralized but provided by a complex network of public bodies at law and a large number of independent regional and local bodies. Because the German healthcare system differs significantly from others, the transferability of results of international studies still needs to be verified.

### Objectives

The objective of the trial is to evaluate the effectiveness of TBHC for patients of a health insurance fund against usual care regarding its impact on healthcare costs and patient-reported outcomes. The primary hypothesis is that TBHC will extend the time period until hospital readmission. Secondly, we hypothesize that TBHC will reduce healthcare costs and hospital readmission rates.

Furthermore, the positive impact of TBHC on patient-reported outcomes like quality of life (QoL), depression and anxiety, health behavior, health literacy, patient activation and the evaluation of TBHC by participants will be evaluated. We also expect TBHC to increase quality of life and decrease psychological distress such as depression or anxiety.

## Methods/Design

### Study design

The study is a prospective randomized controlled trial (RCT) comparing TBHC with patients in usual care during a 4-year time period. There are three follow-up measures; in addition to the baseline measure ( $T_0$ ) the data will be assessed again at 12 months ( $T_1$ ), 24 months ( $T_2$ ) and 36 months ( $T_3$ ). The length of the coaching will be tailored to the needs of the patient, but will not exceed two years.

The studies comply with the Helsinki Declaration 2008. The ethics approval was granted by the Hamburg Medical Chamber Ethics Committee.

### Sample procedures

#### Inclusion criteria for patients

Participants should be at least 18 years old and insured of the KKH statutory health insurance. Moreover, included patients will need to have one or more diagnoses of the following: diabetes, coronary artery disease, asthma, hypertension, heart failure, chronic obstructive pulmonary disease (COPD), chronic depression or schizophrenia. Additional inclusion criteria will be used for each target disease. For example, for patients with type 2 diabetes, hypertension or coronary artery diseases, a risk score for hospital readmission will be calculated. Based on various variables from routine data a logistic regression model was designed to predict hospital readmission using SPSS 19. Those variables are, for example, healthcare costs, international classification of diseases (ICD)-diagnoses, age and gender. This model has been validated by analyzing the receiver operating characteristic curve (ROC) [26] and the positive predictive value [27] and showed valid predictions. If the calculated risk for hospital readmission within the next year is higher than 50%, the person will be included in the study. Patients will be excluded from the study if they have insufficient German language skills, are hard of hearing or are not able to read or use a phone.

### Study procedures

The eligible insureds will be randomized to the intervention and control group. After randomization, members of the intervention group will receive an invitation to take part in the TBHC and an acquisition call. If they send back the confirmation of participation, they will be included in the study as participants. In case they

will not send back the required confirmation, insureds will be grouped as decliners. The control group will receive no invitation.

After completion of the treatment allocation, envelopes will be sent out to the members of the three groups. The first mailing consists of a cover letter, an explanation of the study, information regarding privacy, an informed consent and the questionnaire itself. Six weeks after the first letter, a reminder will be sent out with the same content. In order to limit expenses, just 50% of the decliners who will be randomly selected will receive an envelope (Figure 1).

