## Description of the intervention and control condition

### Intervention condition

The TBHC will follow the concepts of motivational interviewing techniques, individual, collaborative goal setting and shared decision-making. The coach will lead the conversation, but will try to follow a non-directive approach. There will be a minimum frequency defined as one telephone contact every six weeks. The TBHC will have a maximum duration of two years. The intervention will be tailored to chronic diseases that are in need of similar self-management strategies: 1) asthma and COPD, 2) type 2 diabetes, hypertension and coronary artery disease, 3) heart failure and 4) depression and schizophrenia. Each of these disease-specific implementations of the TBHC intervention will have its own treatment manual. These manuals will include information about the inclusion criteria, the scientific background of the campaign and its key contents. All components of the campaign such as the coaching process will be described as well. For example, there will be instructions for specific coaching situations and main topics (for example, diet, immunization and foot control in diabetes and complementary medicine). Even though these instructions exist, the coaching will be tailored to the patients' needs and his individual medical condition. Additionally, the coaches will be supported by a web library and a software program. The web library will provide health information to the coaches to ensure that the information given is evidence-based and up-to-date (for example, by referring to actual

clinical practice guidelines). The software contains available printed information material such as education leaflets for specific conditions, medication plans and weight-control tables that can be sent to the participants by mail. The software also offers a tool to document the process, individual goals, medication, clinical parameters (like HbA1c or blood pressure) and diagnoses.

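### The T0 questionnaire is mailed after randomisation and after contact with the intervention arm only, so it is not assured to be a pre-treatment baseline for the secondary patient-reported outcomes

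*Protocol*

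**What the plan says.** The protocol (Abstract) describes a conventional schedule: "Data are collected at baseline and after 12, 24 and 36 months". Study design labels the first measurement T0, the baseline.

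Study procedures gives the order of events:

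1. "The eligible insureds will be randomized to the intervention and control group".
2. "After randomization, members of the intervention group will receive an invitation to take part in the TBHC and an acquisition call". Controls are not invited.
3. Intervention members who return a confirmation become participants; the others become decliners.
4. "After completion of the treatment allocation, envelopes will be sent out to the members of the three groups". This first mailing contains the study information, the consent form and the questionnaire. Half of the decliners are sampled for it.
5. "Six weeks after the first letter, a reminder will be sent out with the same content".

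On coaching itself, the Intervention condition section says: "There will be a minimum frequency defined as one telephone contact every six weeks". It sets a maximum of two years but gives no date for the first call. Treatment allocation states that nobody is blinded after assignment, that decliners get no coaching, and that coaches are not told who answers the survey. Secondary outcomes describes the patient-reported outcomes largely as changes. Statistical analysis names ANOVA and ANCOVA for them without saying whether T0 is the covariate.

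**The concern.** A baseline can be subtracted or adjusted for because treatment assignment cannot have influenced it. Measured before randomisation, it differs between arms only by chance. The order above does not give that property. When the questionnaire reaches an intervention member, that person has been invited, called and asked to decide about coaching. A control has had no contact.

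Mood, motivation, stage of change, adherence and smoking are self-reported and could respond to such contact. If they do, the T0 difference between arms contains a consequence of assignment, and subtracting it or adjusting for it carries that consequence into the estimated effect. A T0 imbalance could then not be read as chance. The rule to adjust for covariates where groups differ significantly would, if applied to T0 values, adjust for such a difference. The Discussion acknowledges that randomisation preceded consent, and the bias this may bring to the two analyses without decliners. It does not mention the position of T0.

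**Working it through.** **Can T0 precede the contact?** The mailing goes to three groups: participants, decliners and controls. The first two exist only once coaching has been accepted or refused, so the mailing follows the invitation and call. No other questionnaire is described that could serve as T0.

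**Is T0 assured to precede coaching?** No rule holds the first call until T0 is back. Coaches do not know who responds, so they could not apply one. The assumed response rate is 18% to 40%, while routine-data outcomes cover everyone randomised, so coaching cannot depend on a returned form. Only a fixed waiting period could protect T0, and none is stated. But no start date is stated either. The reminder falls one minimum call interval (six weeks) after the first letter; whether a call has taken place by then depends on a start date that is not given.

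**Who is affected?** About 65% are expected to decline (Power calculation). Their T0 can be influenced only by the invitation and call. Coaching could influence only the T0 of participants.

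**The plan's own figure.** Power calculation gives 1,670 patients for d = 0.2 at T2, two-sided 5%, 95% power. For an allocation ratio k, total N = (1 + k)²/k × (1.960 + 1.645)²/0.2² = (1 + k)²/k × 324.9:
- k = 1: 1,300
- k = 5: 2,340
- k = 2.78: 1,670

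The figure fits an analysed ratio near 2.8. That is plausible, since half the decliners are not surveyed and response differs by group, but the text does not state it and Figure 1 is not shown. The point does not rest on this number. What matters is that d is a group difference at T2, not a change from T0.

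**Illustration of size.** Assumptions, none from the document: every participant's T0 comes back six weeks into coaching, and benefit builds up linearly over W weeks. The share already present at T0 is f = 6/W. A change score then estimates d(1 − f). ANCOVA on T0 with slope ρ estimates d(1 − ρf). With d = 0.20 and ρ = 0.5 to 0.7:

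| W (weeks) | f | Change score | ANCOVA on T0 |
|---|---|---|---|
| 104 | 0.058 | 0.188 | 0.194 to 0.192 |
| 52 | 0.115 | 0.177 | 0.188 to 0.184 |
| 26 | 0.231 | 0.154 | 0.177 to 0.168 |

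If only a share q of forms is that late, the change-score loss is q × f. For q = 30% to 60% it runs from 0.30 × 0.058 = 1.7% to 0.60 × 0.231 = 13.9%, so d becomes about 0.197 to 0.172. If coaching starts after T0, f = 0. If early contact lowers self-ratings, f is negative and the change score overstates the effect. Decliners do not alter the proportional loss from coaching, because they add neither coaching effect nor coaching contamination.

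**What does not use T0.** Time to readmission, service use and costs come from insurance data. The propensity scores use insurance data from the year before recruitment.

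**The case against.** The strongest objection is that the protocol nowhere says coaching has begun when T0 is mailed or returned. A minimum call frequency is not a start date, and start-up rules could sit in the disease-specific manuals, which are not shown. This stands. A reader might infer that T0 in the intervention arm is taken after treatment has started; the document supports only that nothing assures the reverse. That reading is also too broad for an arm in which about 65% are expected to receive no coaching.

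A reader might also infer that the coaching effect is understated by a definite amount, for example 30% if 60% of forms are late and half of the two-year effect is present by then (0.60 × 0.50). Neither input is in the document. Half of the effect after about one contact is hard to defend in a programme of roughly 17 calls at minimum frequency (104/6 = 17.3). The direction is open too, since agreeing to be coached could move self-reports either way. Nor should the shrinkage be applied to the planned d = 0.20 as lost power, because that contrast is defined at T2.

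It is also fair that the role of T0 in the analysis may be settled in a statistical analysis plan that is not at hand. But such a plan cannot change the order of mailing, and outcomes framed as changes need a baseline. The order is fixed in the protocol, and following it produces the problem.

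**Conclusion.** The point holds in limited form. T0 is not pre-randomisation, it follows contact that only one arm received, and it is not assured to precede coaching in participants. Change from T0, or adjustment for T0, may therefore distort the comparison on the secondary patient-reported outcomes.

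Neither the size nor the direction follows from the document. The 6% to 23% loss in the table is conditional on its stated assumptions, and zero loss is equally compatible with the text. The primary outcome, the cost outcomes and an unadjusted comparison of observed T2 values are unaffected. The one qualification is that last observation carried forward, listed only as an example for missing data, would bring T0 values back into a T2 comparison. This is a cheap improvement and does not threaten the trial's main conclusion.

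**What to change.** **Patients still to be recruited** (recruitment is expected to run to September 2014): mail T0 to both arms at the same time relative to randomisation, before the invitation and acquisition call. Controls already receive the questionnaire without a coaching invitation, so the present order is not forced. Do not make the start of coaching depend on the return of T0. That could delay coaching while the primary outcome's clock runs from enrolment, and it could reveal to coaches who responds. Forms returned after the reminder may still follow contact, so date these as well.

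**Patients already enrolled:** record the T0 completion date against the first-call date; the coaching software already documents the process. Do not treat forms completed after the first call as baseline, but keep those patients in the analysis, since dropping them would select on events after randomisation. Add an analysis of T2 values by randomised group, adjusted for pre-randomisation routine data instead of T0.

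**Cost:** one extra analysis and some postage. At 5:1, 12,000 × 5/6 = 10,000 intervention members; 65% decline = 6,500; the half not now surveyed = 3,250. (12,000 − 3,250 = 8,750, close to the stated 9,000 invited to the survey.) Surveying all later decliners at T0 adds about 3,250 first mailings and up to 3,250 reminders, at most about 6,500 envelopes.

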### Treatment allocation

To ensure comparability between the intervention and the control group, a stratified random allocation design will be used based on sociodemographic values with a 5:1 allocation ratio to intervention and control group. The randomized intervention group consists of participants and decliners. The decliners will not receive any TBHC. However, they will have the opportunity to opt in to the TBHC via a telephone number printed on the questionnaires. In that case, they will be excluded from the study.

Once the patients are assigned to one of the three groups there will be no blinding of coaches, patients or researchers and their assistants. Nevertheless, the coaches will not know who is responding in the study. The questionnaires are pseudonymized.

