### Power calculation

Calculation of the target sample size was based on the patient reported outcomes collected by questionnaire. In order to achieve a power of at least 95% at a type I error rate of  $\alpha = 5\%$  in a two-sided test accounting for the unbalanced group allocation, a minimum of 1,670 patients are needed to be able to detect a small standardized mean difference in group comparisons (Cohen's  $d$  of 0.2) [28] at  $T_2$  following the intention-to-treat principle. Assuming a response rate between 18% and 40% and drop-out rates between 10% and 82% depending on group and phase, a target sample size of approximately 9,000 patients was identified who should be invited to the questionnaire survey. Assuming that around 65% of the invited patients will decline participation and half of them will be followed up, a total of 12,000 patients were targeted (see Figure 1). Because the primary outcome 'time until hospital readmission' is collected from routine data available for the total sample of 12,000 patients from the KKH statutory health insurance, the primary analysis is sufficiently powered to detect even very small effects with a high probability (low type II error).

[figure not shown]

**Figure 1** Expected participant flow for patient-reported outcomes.

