### Statistical analysis

Following the intention-to-treat approach we will include all randomized participants in the primary analyses in order to avoid biases such as non-random attrition of participants. As many of the randomized participants decline to take part in the TBHC we run a second intention-to-treat approach, testing the participants versus the control group. Additionally we will perform a sensitivity analysis following the as-treated approach including only participants that have received a minimum of five coaching calls.

Therefore, three different analyses will be performed:

- 1) Intention-to-treat 1: comparing the randomized intervention group (including decliners) versus the control group.
- 2) Intention-to-treat 2: comparing those who took part in the intervention versus the control group (excluding the decliners).
- 3) As-treated: comparing participants who received a minimum of five calls versus the control group.

In order to enhance the comparability of intervention group and control group in the health economic outcomes for analyses 2 and 3, propensity score matching (PSM) will be used to control potential confounding. Routine data from the 12-month period preceding recruitment will be used to match individuals in the intervention group with controls by means of propensity scores. Formally, the propensity score is a person's probability of being assigned to the intervention group given a set of observed covariates. The covariates in the propensity score model will be based on routine data: for example, age, sex, ICD diagnoses, number of days spent in hospital and healthcare costs in the preceding year. The predicted probabilities of unconditional logistic regression models with 'treatment' (intervention versus controls) as dependent variable and the described set of covariates are the basis for the subsequent matching of both groups.

For the primary outcome 'time until hospital readmission' we will use the hazard ratio from a proportional hazard model. Service use and costs will be analyzed by logistic and linear random effects regression models using bootstrapped standard errors.

The secondary outcomes that are patient reported will include different scales, instruments and items with various scale levels. For the analyses of nominal scaled outcomes we will use chi-square tests. Ordinal and interval scaled outcomes will be analyzed using ANOVA

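### Only half of the decliners are surveyed, but the stated ITT-1 analyses of patient-reported outcomes carry no sampling weight, so coached participants are over-represented in the intervention arm

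*Protocol*

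**What the plan says.** Protocol, Treatment allocation: patients are randomized "with a 5:1 allocation ratio to intervention and control group". "The randomized intervention group consists of participants and decliners", and "The decliners will not receive any TBHC".

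Protocol, Study procedures: to save expense, "just 50% of the decliners who will be randomly selected will receive an envelope". No subsampling is described for participants or controls.

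Protocol, Power calculation: the uptake assumption reads "Assuming that around 65% of the invited patients will decline participation and half of them will be followed up". On that basis "a total of 12,000 patients were targeted", of whom about 9,000 are to be sent the questionnaire. The sample size is set on a patient-reported outcome at 24 months under intention to treat. Losses are given only as a range: "Assuming a response rate between 18% and 40% and drop-out rates between 10% and 82% depending on group and phase".

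Protocol, Statistical analysis: the first of three analyses is "Intention-to-treat 1: comparing the randomized intervention group (including decliners) versus the control group". Patient-reported outcomes are to be analysed by chi-square tests, ANOVA and ANCOVA. Covariate adjustment follows if groups differ significantly, and at least two missing-data procedures are planned. Propensity score matching is reserved for the health economic outcomes in analyses 2 and 3. A weight for the halved decliner sample is not mentioned.

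Protocol, Discussion: the limitations accept that participants and decliners probably differ, but name a resulting bias only for ITT-2 and the as-treated analysis.

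**The concern.** The survey design and the ITT-1 contrast do not fit together. Decliners are part of the randomized intervention arm and receive no coaching, so they dilute any coaching effect in a true intention-to-treat comparison. Surveying only half of them removes part of that dilution. The control arm contains people who would have accepted and people who would have declined, and it is not thinned in the same way.

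Two things are at stake in an unweighted comparison. First, the treatment effect is averaged over a mix with more uptake than was randomized. Second, if participants and decliners would differ at follow-up even without coaching, part of that difference enters the estimate. The Discussion leaves the impression that ITT-1 is protected from participant-decliner bias. That is true for routine-data outcomes but not for questionnaire outcomes.

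**Working it through.** **Inputs.** 12,000 randomized, 65% declining, half of the decliners followed up, response 18-40%, power 95%, two-sided alpha 5%, d = 0.2 and N = 1,670 (Power calculation); 5:1 allocation (Treatment allocation).

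**1. The protocol's own survey size.**
- Intervention 12,000 × 5/6 = 10,000; control 2,000.
- Participants 0.35 × 10,000 = 3,500; decliners 6,500, of whom 3,250 are surveyed.
- Surveyed: 3,500 + 3,250 + 2,000 = 8,750, within 3% of the stated 9,000 or so. This reading of the flow matches the protocol.

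**2. Participant share of the intervention arm, equal response.**
- Randomized: 3,500/10,000 = 0.350.
- Surveyed: 3,500/(3,500 + 3,250) = 0.519.
- If coaching changes the outcome by τ in participants and by nothing in decliners, the ITT effect is 0.35τ and the unweighted estimate is 0.519τ. The ratio is 0.519/0.35 = 1.48, so a true 0.20 SD would appear as 0.296 SD.

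**3. Unequal response.** The text gives no split by group, so both extremes are assumed.

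| Response, participants / decliners | Unweighted share | Ratio to 0.35 | Share with weight 2 |
|---|---|---|---|
| equal | 0.519 | 1.48 | 0.350 |
| 40% / 18% | 1,400/(1,400 + 585) = 0.705 | 2.0 | 1,400/(1,400 + 1,170) = 0.545 |
| 18% / 40% | 630/(630 + 1,300) = 0.326 | 0.93 | 630/(630 + 2,600) = 0.195 |

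The weight of 2 is exact for the sampling step and does nothing for non-response. In the last row the two distortions nearly cancel by chance, and removing only one of them moves the share further from 0.35.

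**4. Participant-decliner difference δ at follow-up, not due to coaching and not explained by baseline.**
- Bias = (share − 0.35) × δ. With equal response this is 0.169δ, or 0.034 SD for an assumed δ of 0.2 SD.
- The standard error implied by the power statement is 0.2/(1.960 + 1.645) = 0.0555, so the shift is 0.0337/0.0555 = 0.61 standard errors.
- Type I error at an unadjusted two-sided 0.05: 1 − Φ(1.960 − 0.61) + Φ(−1.960 − 0.61) = about 9%.
- For assumed δ from 0.1 to 0.5 SD the bias is 0.017 to 0.084 SD and the type I error about 6% to 33%.

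**5. Price of weighting.**
- Variance factor in the intervention arm: 0.35²/0.519 + 0.65²/0.481 = 1.11 for the sampling weight with equal response. With response weights at 40%/18% it is 0.35²/0.705 + 0.65²/0.295 = 1.61.
- N = 1,670 corresponds to 95% power at a group ratio of about 2.78:1, which may be the expected ratio of responders at 24 months. The participant-flow figure is not visible, so this cannot be confirmed. At that ratio, a variance factor of 1.11 lowers power from 95.0% to 94.4%.

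**The case against.** The protocol does not reject weights; it is silent about them. A known sampling fraction is something an analysis plan could handle, and that plan is not at hand. This stands as a limit on the claim: the protocol cannot be said to have chosen an unweighted analysis. It does not dispose of the point, because the protocol itself fixes the unequal sampling, the ITT-1 contrast and the tests, and its limitations leave ITT-1 out.

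Several stronger readings are tempting, and the document does not support them:

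- A reader might infer that every baseline difference between volunteers and decliners becomes a false effect. Patient-reported outcomes are described as changes, there is a baseline measurement, and ANCOVA is among the methods. A stable gap in level is largely removed by change scores or baseline adjustment. What remains is a difference in course. Baseline adjustment does not, however, restore the 35:65 mix over which the treatment effect is averaged.
- A reader might infer that differential response can only worsen the distortion. The reverse split gives a factor of 0.93. The stated drop-out of 10-82% could also move the share in either direction.
- A reader might take a type I error of 9%, or up to 25% at 40%/18% response, as the plan's error rate. These figures rest on an assumed 0.2 SD gap that survives to follow-up, before the planned Bonferroni correction. With three comparisons (an assumption; alpha 0.0167), 9% becomes about 4%. That is still above its nominal level, but far less striking.

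It is also fair to say that controls who answer are a self-selected minority too, and that non-response in all groups may matter more than the 50% subsample. The unsampled decliners are a random half, so imputation that uses decliner status could also address the problem, but the protocol does not specify this.

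**Conclusion.** The point holds in a limited form. Followed as written, the ITT-1 comparison of patient-reported outcomes does not estimate the effect in the randomized intervention arm. With equal response, an effect confined to participants is overstated 1.48-fold. Over the extremes of the stated response range the factor is about 0.93 to 2.0, with the group split assumed. The additional selection term is about 0.17 times any follow-up difference that baseline does not explain. Its sign is unknown, and it could offset the inflation as well as add to it.

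A reader might infer that the trial's main result is at risk. It is not: the primary outcome and the economic outcomes come from routine data on the whole randomized sample, with no subsampling. The questionnaire comparison does matter, because the sample size was derived from it. The correction is cheap and can be made at analysis, so this should be fixed, but it does not undermine the primary analysis.

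**What to change.** - In every ITT-1 patient-reported analysis, give sampled decliners a weight of 2 (the inverse of the 50% sampling fraction), use robust standard errors, and adjust for the baseline value. Report the unweighted result as a sensitivity analysis.
- Where the pseudonymized questionnaire and routine data can be linked, add response weights fitted separately in each group from pre-randomization routine data, as a sensitivity analysis. The protocol describes no such linkage, so its feasibility has to be confirmed first. This step matters because the weight of 2 leaves differential response uncorrected and could, under one extreme split, expose it more.
- Extend the limitation in the Discussion on participant-decliner differences to the ITT-1 patient-reported outcomes.

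Cost: wording and a simple weight, with no new data collection for the sampling weight. Intervention-arm variance rises by a factor of about 1.11 with equal response (power about 95.0% to 94.4%), and by up to about 1.6 with response weights at an assumed 40%/18% split.
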